**Figure 1 F1:**
[figure not shown]
**Trial protocol overview**. ACS: Acute Coronary Syndrome; dHMR: Directed Home Medicines Review; GP: General Practitioner; AP: Accredited Pharmacist.

**Figure 2 F2:**
[figure not shown]
**Summary of the Lemmens *et al. *framework **[28]. This representation of the 'Evaluation model for disease-management programs' has been adjusted slightly from the originally produced model to better reflect the points of the framework that we consider relevant to the HMR service (shown in further detail through Figure 3). It is important to recognize that this framework highlights the importance of considering patient-related factors, professional-related factors, and health-system factors in both the design and evaluation of interventions targeted toward improving the management of chronic diseases. These considerations have been particularly important throughout the development of this trial.

**Figure 3 F3:**
[figure not shown]
**How the proposed dHMR service addresses the specific components of the Lemmens *et al. *framework **[28]. ACS: Acute Coronary Syndrome; dHMR: Directed Home Medicines Review; GP: General Practitioner; QOL: Quality Of Life. The blue text highlights the areas of the framework where we are investigating the effect of a dHMR with specific detail provided for clarification.

This representation of the 'Evaluation model for disease-management programs' has been adjusted slightly from the originally produced model to better reflect the points of the framework that we consider relevant to the HMR service (shown in further detail in Figure 3). It is important to recognize that this framework highlights the importance of considering patient-related factors, professional-related factors, and health-system factors in both the design and evaluation of interventions targeted toward improving the management of chronic diseases. These considerations have been particularly important throughout the development of this trial

### Setting

Patient enrolment and dHMR referral will be from the two major tertiary referral hospitals in Tasmania, Australia. The Royal Hobart Hospital (RHH) is a 490-bed hospital with an 8-bed coronary care unit (CCU), percutaneous coronary intervention (PCI), and coronary artery bypass grafting (CABG) facilities, and accepts patients from across the state for CABG referrals [29]. The Launceston General Hospital (LGH) is a 300-bed hospital with a 4-bed coronary care unit and PCI facilities [30]. Both hospitals run cardiac rehabilitation programs that are offered to all ACS patients. Patients admitted to these centers generally receive verbal and written education regarding lifestyle changes following ACS from nurses, and medication counseling from nurses or pharmacists, prior to discharge.

### Inclusion/Exclusion criteria

All patients aged 18 to 80 years with a primary diagnosis of ACS presenting at the RHH and LGH will be considered for enrolment into the trial. The wide age range has been chosen to detect differences in the discharge management of patients across different age groups and to examine the suitability of the dHMR intervention across different age groups. The former problem has been previously recognized as an area for further interventional focus by Alexander *et al. *in the CRUSADE trial [31] and the latter has been recognized as an area requiring further investigation through a qualitative review of the HMR service [15].

Patients will be excluded from trial enrolment if they: are not returning to their home following hospital discharge (as this is a requirement of the existing HMR service); are non-Medicare eligible (for example, not a permanent Australian resident); have been diagnosed with a level of cognitive impairment such that the process of informed consent may be obscured; or have been diagnosed with a malignancy that is expected to be terminal within 12 months.

### Randomization

We will use a computer-generated random sequence to provide the randomization coding. Patients will be randomized to the control or intervention groups following computerized recognition that the patient meets the inclusion criteria and has consented to trial involvement. The correct entry of this information into the central trial database will then enable the enrolling researcher to unlock the randomization status for that participant.

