### Intervention

Patients in the intervention group will receive a dHMR at approximately two months following discharge as well as usual care. The time of two months post-discharge was selected as previous studies of ACS patients have demonstrated that the period between one and three months post discharge is when patients are most vulnerable for medication discontinuation [2,3,32]. This suggests that a service addressing both the educational and clinical management aspects of therapy may be most beneficial when offered in this time period.

Based on the existing funding arrangements and recommended reasons for referral, the HMR service is currently available in Australia for all ACS patients following hospital discharge [16]. The uptake of this service, however, may be largely limited by the absence of HMR referral systems in this transitional period. Furthermore, the currently available service could be tailored to maximize the potential for benefit from this service in the ACS population. We propose to add to the existing HMR service in several ways, making the proposed dHMR service more directed toward the ACS population.

Typically, HMRs are ordered by a referral letter generated by the patient's GP. Referral letters may vary significantly in their level of detail, potentially leaving the pharmacist with little direction prior to the patient interview. This concern was highlighted as a potential downfall of the service in a qualitative review that was conducted in 2008 [15]. To address this issue, the enrolling researchers will use a specifically designed database that allows baseline data collection to automatically populate sections of the HMR referral. The referral letter will still be sent to the GP for approval and addition of any further information, such as medications that have changed since discharge. GP approval is a requirement for payment under the existing public service arrangements, and having the GP engaged with the intervention early should increase their willingness to participate. This new approach, however, relieves the GP from having to complete most of the referral data and allows for simple addition of only useful information. The GP may also find the information on this referral letter useful when they receive the letter, as previous research has demonstrated that standard discharge letters following ACS admissions do not always contain a sufficient level of information and sometimes take too long to reach the GP [3].

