### Primary outcome

The primary outcome will be the proportion of patients who are adherent to a complete, guideline-based ACS medication regimen at the trial endpoints. The accepted definition of adherence for this trial will be a medication possession ratio (MPR) of 80% to 120% for all guideline-based medications, which is a commonly accepted cut-off for this measure [35-39]. MPR will be determined by dividing the total number of days of medication supplied by the total specified time period. This value can be multiplied by 100 in order to be reported as a percentage of the time that the patient had medication available to take, a commonly used surrogate measure of adherence. During the baseline interview, we intend to record all possible pharmacies that a patient may attend in order to make the dispensing records complete. If, however, there is a significant shortfall in the completeness of dispensing records, we will use self-report of medication adherence as an alternate measure. The four-item Morisky adherence questionnaire will be used for this purpose [40]. This is a well-validated instrument, being used previously with good predictive validity in patients at risk of cardiovascular disease [40,41]. In the case where a patient has a clearly documented contraindication to one of the four guideline-based medication classes, their medication regimen may still be considered 'complete' provided they are taking all other guideline-based medications. For example, a patient with asthma not taking a beta-blocker but still taking aspirin, an ACE inhibitor, and a statin, will be considered in the same group as those prescribed all four medications. This primary outcome comprehensively assesses the overall impact of the intervention on both GP prescribing behaviors and patient medication-taking behaviors. In order to separately measure the recognized problem of persistence with guideline-based medications, we will complete a secondary analysis of the primary outcome in the group of patients who are prescribed a complete, guideline-based medication regimen at the time of discharge from hospital.

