### Data collection

Baseline data collection will occur in hospital at the time of enrolment, immediately post-discharge from hospital and at six weeks post-discharge - when the participants will be sent their first questionnaire set. The in-hospital baseline data collection will include the recording of traditional coronary risk factors, as well as the 'cholesterol' version of the INTERHEART Modifiable Risk Score (IHMRS) [64]. This will allow for baseline comparison of risk between the two groups. Although not validated to calculate risk in a population of patients following a coronary event, the IHMRS requires the recording of risk factors in a way which emphasizes their correlation to their level of actual risk and this remains relevant, regardless of the patient's degree of heart disease. For example, the IHMRS requires the recording of smoking status into several cutoffs depending on the number of cigarettes smoked per day, which correlates independently to heart attack risk, as opposed to simply recording cigarette smoking status in an arbitrary fashion, which is of lesser value with regard to risk comparisons. The final baseline data collection point of six weeks post-discharge for questionnaire mail-out reflects our intention to gauge each patient's status on each of the questionnaires in the time directly before the HMR and not while in hospital, as factors, such as adherence behavior, may be very high in hospital but may significantly decline over time following discharge [2,3,14,65,66]. Patients in the intervention group will be asked to ensure that they complete their questionnaire before their pharmacist visit and pharmacists will record whether or not this has happened as reported by the patient. Patients in the control group will be given a reminder telephone call if their questionnaires have not been returned by three weeks from the mail-out date.

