Although based on an existing, Medicare-funded service, the treatment protocol faces several potential barriers to success. Largely, this includes interprofessional barriers, such as GP approval of the dHMR referrals and GP acceptance of pharmacists' recommendations. The former point will be aided by the enrolling researcher contacting the GP once randomization has been revealed. Although GP approval of dHMR referrals may affect the uptake of the intervention in this trial, the use of a consistent and informative referral letter and a telephone conversation to support this letter, could prove to be advantageous over the current systems for initiating standard HMR referrals, which may not always be this well-structured. The other barrier of GPs not accepting pharmacists' recommendations has been raised due to previous research showing that GPs only action approximately 45% of pharmacist's recommendations following HMRs [68,69]. The educational material provided to accredited pharmacists completing this trial, however, should help guide pharmacists to make recommendations which will be relevant post-ACS and simple to implement. Furthermore, as the education package has been based on the latest evidence in ACS management, even if GPs do not accept all of the pharmacists' recommendations, they should still be gaining useful information from the dHMR reports. This may lead to improved ACS management, irrespective of the rate at which GPs accept pharmacists' individual recommendations.

Having the pharmacists complete the online training package may also be another barrier to the successful implementation of the trial protocol. The education and assessment package should take approximately three hours to complete and will be rewarded with recognition of continuing professional development and an AUD$50 honorarium. We hope that these incentives and the easy-to-use format of the material will help facilitate the completion of the package. Through careful consideration of the potential barriers recognized above, the dHMR processes that we have developed have transformed these barriers into opportunities to improve the implementation of the intervention.

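### The release rule lets allocation be unlocked on eligibility and consent, so the pharmacy list behind the primary outcome may be recorded with the arm known

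*Protocol article*

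**What the plan says.** All references are to the protocol article.

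- **Randomization.** Patients are randomized "following computerized recognition that the patient meets the inclusion criteria and has consented to trial involvement". Correct entry of that information "will then enable the enrolling researcher to unlock the randomization status for that participant". No other condition for release is named.
- **Intervention.** The section says that "the enrolling researchers will use a specifically designed database that allows baseline data collection to automatically populate sections of the HMR referral". The referral letter belongs to the intervention arm only.
- **Discussion.** GP approval is to be helped by "the enrolling researcher contacting the GP once randomization has been revealed", so the person who enrols also learns the arm and acts on it.
- **Primary outcome.** "During the baseline interview, we intend to record all possible pharmacies that a patient may attend in order to make the dispensing records complete". Adherence means an MPR of 80% to 120% for all guideline-based medications, where MPR is days supplied divided by the length of the period. If dispensing records fall significantly short, a four-item self-report questionnaire is used instead.
- **Data collection.** "Baseline data collection will occur in hospital at the time of enrolment, immediately post-discharge from hospital and at six weeks post-discharge". The in-hospital part covers traditional coronary risk factors and a modifiable risk score that grades smoking. At six and twelve months, community pharmacies are asked for dispensing records.
- **Outcomes.** Blinded assessment is stated for the two endpoints, six and twelve months.
- **Trial status.** Recruitment had not started.

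**The concern.** The release rule is stated in positive terms: once eligibility and consent are in the database, the arm can be seen. Baseline recording is not part of the gate. Under that rule, the same researcher may look up the arm and then conduct or complete the baseline interview.

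This matters most for the pharmacy list. The list decides where dispensing records are requested. Supply from a pharmacy that is not on it is not counted, so the MPR for that medicine falls. Because every guideline-based class must lie within 80% to 120%, one class falling below 80% is enough to make the patient non-adherent. If lists were fuller in one arm, measured adherence would differ between arms with no true effect. A fuller intervention list would inflate the result, and a fuller control list would mask a real effect.

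Blinding at the endpoints does not reach this, because a blinded assessor still works from records requested with that list. The self-report fallback needs a noticeable shortfall, and a pharmacy nobody listed may leave no visible gap.

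Baseline smoking and risk data are exposed in the same way. Smoking at baseline is the reference for the cessation outcome. The risk score is meant for comparing the groups at baseline. Under Statistical analysis, baseline differences can enter the multivariate model when the primary result is significant.

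**Working it through.** **Step 1. Order of events.** The sections were compared on one question: must the baseline interview precede the unlock?

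| Section | What it fixes | Order relative to unlock |
|---|---|---|
| Randomization | Eligibility and consent entered, then unlock available | Names only these two conditions |
| Primary outcome | Pharmacies recorded at the baseline interview | Not stated |
| Data collection | First baseline data in hospital at enrolment | Not stated |
| Data collection | Further baseline data just after discharge | After in-hospital enrolment, so ordinarily after allocation |
| Discussion | GP contacted after the arm is revealed | After unlock |

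No section requires the interview to come first, and none says that it comes second. The order is open.

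**Step 2. The plan's own sample size.** Inputs from Sample size: 45% against 60%, alpha 0.05, power 80%. Two-sided testing is assumed, as the article does not state it.

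- Without continuity correction: n = [1.960 × √(2 × 0.525 × 0.475) + 0.842 × √(0.45 × 0.55 + 0.60 × 0.40)]² / 0.15² = 172.8, so 173 per group.
- With continuity correction: (172.8 / 4) × [1 + √(1 + 4 / (172.8 × 0.15))]² = 185.9, so 186 per group, as stated.
- Dropout: 372 / 0.80 = 465, as stated.

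These figures are not in dispute. The 186 is used below.

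**Step 3. What unequal lists could do.** Assumptions, none of them in the article:

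- true adherence is 45% in both arms (the plan's control rate), so there is no true effect;
- there are 186 analysed patients per group;
- a share c of patients in each arm has a complete list, unrelated to adherence;
- every incomplete list turns an adherent patient into a non-adherent one (worst case).

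Formulas: observed rate p = 0.45 × c; d = p₁ − p₂; SE = √{[p₁(1 − p₁) + p₂(1 − p₂)] / 186}; two-sided rejection = P(Z > 1.96 − d/SE) + P(Z < −1.96 − d/SE).

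| List complete, one arm vs other | Observed rates | d (points) | SE (points) | d/SE | Rejection |
|---|---|---|---|---|---|
| 98% vs 94% | 44.1% vs 42.3% | 1.8 | 5.14 | 0.35 | 6.4% |
| 97% vs 90% | 43.65% vs 40.5% | 3.2 | 5.12 | 0.62 | 9.4% |
| 98% vs 88% | 44.1% vs 39.6% | 4.5 | 5.11 | 0.88 | 14% |

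The nominal rate is 5%. As a cross-check with a pooled standard error under the null, losing 10% of truly adherent patients in one arm only also gives d = 0.45 × 0.10 = 4.5 points and 14%.

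**The case against.** The best defence is that a journal article condenses its protocol. The Randomization section says that eligibility and consent enable the unlock; it does not call them the only required entries. Field order and form locking often sit in a full protocol or data manual. The text also fits the safe order: in-hospital data are taken at enrolment, and contact with the GP is a separate step after the arm is revealed.

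Much of this stands. A reader might infer that baseline data will be collected by someone who knows the arm. The article does not support that; it leaves the order open.

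A reader might also infer a built-in motive to list pharmacies more fully in the intervention arm, because the database "allows baseline data collection to automatically populate sections of the HMR referral". The article does not say that the pharmacy list is among those sections, and the stated intent to record all possible pharmacies makes no distinction by arm.

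The outcome link has limits too. An omitted pharmacy matters only if the patient uses it and the lost supply takes the MPR of some medicine out of range. With an upper limit of 120%, an omission could even bring an over-supplied patient into range. Self-report replaces dispensing data if the shortfall is significant.

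What does not stand is that nothing needs changing. The article chose to state the release rule, and as stated it is sufficient for unlocking before the interview. That is a rule that can be improved, not merely a detail left out.

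**Conclusion.** The point holds as a weakness in the stated release rule. The rule permits the pharmacy list, smoking status and risk factors to be recorded with the arm known, and neither endpoint blinding nor the self-report fallback would reliably repair a list made that way.

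It does not show that bias will occur. The size is unknown, since the article gives no completeness figure for either arm. Gaps of 4 to 10 points in list completeness would give false differences of 1.8 to 4.5 points and a two-sided error of about 6% to 14%. Those figures rest on 45% true adherence in both arms, 186 per group, and the worst case in which every incomplete list costs an adherent patient that status.

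A reader might go further and infer that allocation concealment is broken. The documents do not support that: the Abstract describes central, computerized sequence generation and concealment, and the arm is released only after eligibility and consent. The issue is how data are recorded after release. The sample size is unaffected.

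**What to change.** Extend the release rule in Randomization: the database releases the allocation only when the in-hospital baseline form, including the pharmacy list, smoking status and risk factors, is complete and locked. Later edits, including pharmacies added during follow-up, are logged with date and arm.

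The lock cannot cover the items collected just after discharge, which follow allocation. Collect these with the same form and the same rule in both arms. The six-week questionnaire also falls after randomization and is outside the lock.

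The cost is a required-field check in a database that already gates randomization, before recruitment has begun. No visits, staff or sample size change. If the full protocol already enforces this order, one sentence in Randomization saying so settles the point.

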### Controls

Following randomization to the control group, patients will be offered the usual care processes involved with post-discharge management of ACS in Australia. Through the public health system, patients are able to attend a cardiac rehabilitation program at their local hospital as well as a cardiologist follow-up appointment, usually occurring at one month following discharge. The cardiac rehabilitation programs from the two different hospitals may vary slightly in their level of physical activity, but the material covered in their information sessions is similar.

### Intervention

Patients in the intervention group will receive a dHMR at approximately two months following discharge as well as usual care. The time of two months post-discharge was selected as previous studies of ACS patients have demonstrated that the period between one and three months post discharge is when patients are most vulnerable for medication discontinuation [2,3,32]. This suggests that a service addressing both the educational and clinical management aspects of therapy may be most beneficial when offered in this time period.

Based on the existing funding arrangements and recommended reasons for referral, the HMR service is currently available in Australia for all ACS patients following hospital discharge [16]. The uptake of this service, however, may be largely limited by the absence of HMR referral systems in this transitional period. Furthermore, the currently available service could be tailored to maximize the potential for benefit from this service in the ACS population. We propose to add to the existing HMR service in several ways, making the proposed dHMR service more directed toward the ACS population.

Typically, HMRs are ordered by a referral letter generated by the patient's GP. Referral letters may vary significantly in their level of detail, potentially leaving the pharmacist with little direction prior to the patient interview. This concern was highlighted as a potential downfall of the service in a qualitative review that was conducted in 2008 [15]. To address this issue, the enrolling researchers will use a specifically designed database that allows baseline data collection to automatically populate sections of the HMR referral. The referral letter will still be sent to the GP for approval and addition of any further information, such as medications that have changed since discharge. GP approval is a requirement for payment under the existing public service arrangements, and having the GP engaged with the intervention early should increase their willingness to participate. This new approach, however, relieves the GP from having to complete most of the referral data and allows for simple addition of only useful information. The GP may also find the information on this referral letter useful when they receive the letter, as previous research has demonstrated that standard discharge letters following ACS admissions do not always contain a sufficient level of information and sometimes take too long to reach the GP [3].

In addition to the specific referral letter, the service will be further directed by offering accredited pharmacists across Tasmania an online education and assessment package. In order for a pharmacist to complete an interventional dHMR according to the trial protocol, they will be required to have a current accreditation status and have successfully completed the education and assessment package. Upon completion of the education and assessment package, accredited pharmacists will gain recognition of continuing professional development and an AUD$50 reimbursement for their time.

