The Home Medicines Review (HMR) program is an existing community-based service that has the potential to be tailored to meet the needs of patients recently discharged from hospital following ACS. Although this potential has not been fully realized in the past [15], HMRs may be used to particularly target patients' persistence and adherence to guideline-based medications following ACS. The HMR service currently involves general practitioner (GP) referral of patients to an HMR-accredited pharmacist, often through a community pharmacist liaison [16]. The accredited pharmacist will visit the patient in their home, discuss their medication taking habits, and provide education or adherence interventions where required. Following the home visit the accredited pharmacist writes a report for the GP noting their observations and any clinical adjustments that could be made to the patient's medication regimen. Based on this report, the GP is expected to complete an agreed management plan, selecting the accredited pharmacist's recommendations which they agree to implement and/or follow up. The service is currently available in Australia, free of charge to Australian citizens under funding arrangements through the public health system, Medicare Australia. The GP, accredited pharmacist, and community pharmacist involved with an HMR service are paid by way of reimbursement from Medicare Australia. One of the eligibility criteria for HMRs is recent hospital discharge [16] and the HMR service has been demonstrated to be feasible as a post-discharge service for patients following ACS in the Australian healthcare setting [17]. However, the effect of this service on clinical outcomes following ACS is unknown.

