### Sample size

We are aiming to detect a change in the primary outcome of 15% between the control and intervention groups. This predicted change is based on the results of the DMACS study, whereby a 12% post-intervention improvement was observed on the proportion of patients taking the same four guideline-based medications at discharge [3]. To detect a change of 15%, assuming a control group result of 45%, a power to detect a difference of 80% with alpha = 0.05, we require a minimum sample size of 186 patients per group. To account for an approximate dropout rate of 20%, we aim to enroll 465 patients in total.

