### Statistical analysis

All baseline variables will be compared between the control and intervention groups using independent samples t-tests for continuous variables and chi-squared analysis for categorical variables. All outcomes will be reported as descriptive comparisons between the control and intervention groups, with significance reported at alpha = 0.05. Where primary outcomes reach statistical significance, any noted difference in the baseline group comparison will be tested by univariate comparison with stepwise addition into a multivariate model for those with univariate significance of *P *< 0.1. Changes in each group's questionnaire results between baseline and study endpoints, as well as differences between intervention and control group's questionnaire results, will be reported. Further correlational investigations between questionnaire results and adherence will be reported elsewhere. As there are several potential barriers that may prevent a patient randomized to the intervention group from receiving a dHMR according to the protocol, we will use both an intention-to-treat analysis as well as an on-treatment sensitivity analysis.

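### The sample size makes no allowance for clustering of intervention patients by visiting pharmacist, so the stated 80% power holds only if that clustering is small

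*Protocol article*

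**What the plan says.** The protocol article randomizes patients individually (Randomization). Its description of the existing Home Medicines Review service, under ACS post-discharge services, makes delivery personal to one professional: "The accredited pharmacist will visit the patient in their home, discuss their medication taking habits, and provide education or adherence interventions where required". The trial version, the directed review (dHMR), keeps that form and adds training: "the service will be further directed by offering accredited pharmacists across Tasmania an online education and assessment package" (Intervention). It states no number of pharmacists and no expected caseload. Control patients receive usual post-discharge care and no trial pharmacist (Controls).

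Under Sample size, the article takes 45% adherent in the control group, a 15-point difference, and "a power to detect a difference of 80% with alpha = 0.05". From this, "we require a minimum sample size of 186 patients per group". The only inflation is for attrition: "To account for an approximate dropout rate of 20%, we aim to enroll 465 patients in total".

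Under Statistical analysis, t-tests and chi-squared tests are named for baseline variables. For outcomes the text is "All outcomes will be reported as descriptive comparisons between the control and intervention groups, with significance reported at alpha = 0.05". Intention-to-treat and on-treatment analyses are both planned, because some intervention patients may not receive a dHMR according to protocol.

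**The concern.** This is a partially nested design. Intervention patients seen by the same pharmacist share that person's interviewing style, clinical judgement and report writing. Control patients share nothing comparable. If pharmacists differ in their effect on adherence, the intervention-arm proportion has a larger variance than the binomial one, and the control proportion does not.

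Some between-pharmacist variation is plausible on the article's own account. The Abstract lists the quality of pharmacists' recommendations among the possible limits on success. Process outcomes includes their recognition of drug-related problems. Data collection accepts that some visits may be made by pharmacists who have not finished the training package, and training status belongs to the pharmacist, not the patient.

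Two things are at stake. The 80% power is stated without condition, although it was computed for independent patients. And if the final comparison ignored pharmacist, its confidence interval could be too narrow.

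**Working it through.** **Inputs from the protocol article (Sample size):** control 0.45, intervention 0.60, alpha 0.05, power 80%, dropout 20%. Sidedness is not stated; two-sided reproduces the planned figure.

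**Step 1: reproduce the planned figure.** The mean proportion is 0.525.
- Without continuity correction: n = [1.96·√(2·0.525·0.475) + 0.8416·√(0.45·0.55 + 0.60·0.40)]² / 0.15² = 172.8, so 173.
- With continuity correction: n' = (172.8/4)·[1 + √(1 + 4/(172.8·0.15))]² = 185.9, so **186**, as stated.
- Dropout: 2·186/(1 − 0.20) = 372/0.8 = **465**, as stated.

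Both figures are fully explained by independent patients plus dropout. No design effect is hidden in them.

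**Step 2: allow for pharmacists in one arm.** The number of pharmacists K, the ICC and the visited fraction f are assumptions, because the documents give none of them. Caseloads are taken as equal.
- Patients per pharmacist: m = 186·f/K.
- Design effect in the intervention arm, with unvisited patients as single units: DE = f·[1 + (m − 1)·ICC] + (1 − f). In the control arm it is 1.
- Type I error of an ordinary uncorrected test that ignores pharmacist: 2·[1 − Φ(1.96/√((DE + 1)/2))].
- Power of a valid uncorrected test: Φ(0.15/√((0.24·DE + 0.2475)/186) − 1.96). The 15-point difference is held fixed throughout, so f changes only the variance.

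**Worked example, K = 20, ICC 0.05, f = 1.** m = 9.3 and DE = 1 + 8.3·0.05 = 1.415. Type I error = 2·[1 − Φ(1.96/√1.2075)] = 7.4 to 7.5%. The standard error is √((0.3396 + 0.2475)/186) = 0.0562, so power = Φ(2.670 − 1.96) = 76%.

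| Pharmacists | ICC | Visited | DE | Type I error if pharmacist is ignored | Power, valid test |
|---|---|---|---|---|---|
| no clustering | 0 | – | 1.00 | 5.0% | 83% |
| 40 | 0.02 | all | 1.07 | 5.4% | 82% |
| 20 | 0.05 | all | 1.42 | 7.4–7.5% | 76% |
| 15 | 0.05 | all | 1.57 | 8.4% | 74% |
| 10 | 0.05 | all | 1.88 | 10.2% | 69% |
| 20 | 0.05 | half | 1.09 | 5.5% | 82% |
| 15 | 0.05 | half | 1.13 | 5.7% | 81% |
| 10 | 0.05 | half | 1.21 | 6.2% | 80% |

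**Step 3: check against the test that gives 186.** With the continuity correction, power with no clustering is 80.0%, so there is no slack. At full uptake and ICC 0.05 it is 76.5% (40 pharmacists), 72.2% (20) and 64.5% (10). The type I error of a corrected test that ignores pharmacist is lower than in the table: 4.8%, 6.0% and 8.5% for the same three cases. The corrected test thus starts below 5% (3.9% with no clustering), which absorbs part of the inflation.

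**The case against.** The strongest reply is that the article does not say the outcome test ignores pharmacist. It names tests for baseline variables only, it is a condensed account, and the handling of provider effects in the variance is ordinary material for an analysis plan that is not at hand. That stands. A reader might infer that all patients will be analysed as independent and that the p-values will be too small. The documents do not support this: it would need an unadjusted outcome test, an ICC above zero and several patients per pharmacist, and none of these is stated.

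The size is also open. Common training with a pass mark and a standard referral letter would tend to make pharmacists more alike. Adherence depends as well on GPs and patients, and the Discussion cites earlier work in which GPs acted on only about 45% of recommendations. These points argue for a low ICC, though not for zero.

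Non-receipt matters too. Unvisited patients stay in the intention-to-treat arm unclustered, and at half uptake most of the inflation disappears. With a continuity-corrected test, the type I error can stay below 5% even with some clustering (4.8% for 40 pharmacists at ICC 0.05).

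What the reply does not reach is the sample size. That is a figure the article fixes itself, and its 80% rests on independence in an arm where the design makes independence doubtful.

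**Conclusion.** The concern holds for the sample size and is conditional for the analysis. Intervention patients are nested within pharmacists, controls are not, and 186 per group (465 in total) contains no allowance for it. The stated 80% power holds only if between-pharmacist variation or caseloads are small. For the uncorrected test, the formula in the working reaches 80% at an intervention-arm design effect of about 1.19 (80.2% at 1.18, 79.8% at 1.20). For the corrected test that reproduces 186, any clustering takes power below 80%.

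Over the assumed values, with an uncorrected test, type I error and power run from about 5.4% and 82% to about 10% and 69%. The unfavourable end needs as few as 10 pharmacists, an ICC of 0.05 and full uptake; at half uptake the same pharmacists and ICC give about 6.2% and 80%. These figures rest on assumed pharmacist numbers, ICC and uptake, on equal caseloads and on a large-sample approximation. They show sensitivity and do not predict this trial's error rates.

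**What to change.** **Analysis.** Take the pharmacist's identity from the dHMR reports, which Data collection already gathers. Analyse the primary comparison by intention to treat in one of two ways, specified in advance:
- a partially nested model with a random pharmacist effect in the intervention arm only; or
- a risk difference with cluster-robust standard errors.

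In either case, treat each control and each unvisited intervention patient as a single unit, and use a small-sample correction because the number of pharmacists may be low. Report the ICC, the number of pharmacists and the spread of caseloads.

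**Sample size section.** State that 80% power assumes no clustering by pharmacist, and give the power over a plausible range of ICC, pharmacist numbers and uptake. No extra enrolment is asked for.

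**Cost.** Some wording in the analysis plan and one added statement on power. The confidence interval may be wider and the stated power less favourable. If the ICC proves negligible, little is lost.
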